| QuantiFERON ® -TB Gold In Tube c                        |                           |                            |                            |                                              | x                         |
| Tuberculin PPD skin test c                                         |                           |                            |                            |                                              | x                         |
| Vital signs (temp, BP, pulse)                                                 | x                         | x                          | x                          | x                                            | x                         |
| Immunology (PBM, plasma)                                                      | x                         | x                          |                            |                                              |                           |
| Clinical observations for signs and
symptoms of TB                         | x                         | x                          | x                          | x                                            | x                         |
| Solicited adverse events (incl. con.
meds.)                                | x                         | x                          |                            |                                              |                           |
| Adverse events (incl. con. meds.)                                             | x                         | x                          |                            |                                              |                           |
| Serious adverse events (incl. con. meds.)                                     | x                         | x                          | x                          | x                                            | x                         |
| Site of injection examination                                                 | x                         | x                          |                            |                                              |                           |
| Diary Review                                                                  | x                         |                            |                            |                                              |                           |

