#### **3.6.2 Clinical Assessments and Laboratory Tests**

An examination of the injection site will be performed 60 minutes after each study vaccine/placebo administration and at 7 and 28 days after each vaccination. Subjects will have CD4+ lymphocyte counts done prior to each vaccination, at 7, 28, and 84 days after each vaccination and then at 6 months post-boost. Vital signs will be recorded prior to each vaccination, at 7, 28, 84 days after each vaccination, and at all subsequent study visits. Subjects will also have tests done for HIV-1 viral load results done prior to each vaccination, at 7 and 28 days after each vaccination, and then at 6 months post-boost.

Blood for hematology and serum chemistry will be collected at screening and prior to booster vaccination and 7 and 28 days after each vaccination. All laboratory samples will be processed according to SOPs provided by the local clinical laboratory.

All subjects randomized to the study will have a Tuberculin PPD skin test and blood for QFT-G collected during screening, and then again at the End of Study visit. Subjects will also be observed for signs and symptoms of TB at every study visit.

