## 5.2 Safety Surveillance During the Study

Subjects will be monitored and safety data collected by way of clinical interviews and examinations, evaluations conducted by study team members, and through reports of laboratory evaluations. Time points and the specific data collected for each of these evaluations are described in protocol appendices.

Through the 28-day period following each vaccination all **adverse events** observed by the investigator (or designee), or reported by the subject spontaneously in response to a direct question, will be medically evaluated and documented in terms of a medical diagnosis on the AE screen.

Through the entire study period all **serious adverse events** observed by the investigator (or designee) or reported by the subject spontaneously or in response to a question will be medically evaluated and documented on the AE screen.

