## 5.6 Definition of Adverse Reaction

An adverse reaction is an adverse event judged to be related to study vaccine (see Section 5.3 for adverse event definition).

**Related adverse events (adverse reactions) are defined as those judged by the investigator or local medical monitor to be possibly, probably, or definitely related to study vaccine.**

**The reporting period for all adverse events and adverse reactions is the 28-day post-vaccination follow-up period.** Adverse events and adverse reactions will be reported using a recognized medical term or diagnosis that accurately reflects the event.

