## 5.7 Solicited Adverse Events and Injection Site Reactions

Solicited adverse events are events the subject is specifically asked about. These adverse events are commonly observed soon after receipt of vaccines. For this study, solicited adverse events include: injection reactions, diarrhea, vomiting and others. Solicited adverse events of local injection site reactions (i.e., pain at injection site, redness at injection site, or swelling at injection site) will be considered causally related to study vaccine (adverse reaction).

**The reporting period during which *solicited* adverse events will be asked of the subject is the immediate 28 day period following each vaccination.** The solicited adverse event reporting period begins with the day of vaccination.

Adverse events and solicited adverse events including assessment of local injection site reactions will be assessed by the investigator for severity, causal relationship to the study vaccine, possible etiologies, and whether the event meets criteria as a serious adverse event (and therefore requires immediate notification to the medical monitor).

Presence of ulceration and/or scarring at the site of injection and axillary lymphadenopathy of the injection arm(s) are considered to be adverse events that are causally related to the study vaccine and are of special interest. Site of injection ulceration (including presence of drainage)

and axillary lymphadenopathy will be actively evaluated during each clinic visit through the end of the study. These events will be recorded on the Adverse Event screen.

In the event that the clinical presentation meets the definition of a serious adverse event, an SAE Report must be completed and the event reported per protocol instructions.

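### Section 5.7 wants ulceration and axillary lymphadenopathy checked at every clinic visit to study end, but the visit schedule and the adverse event reporting period cover only 28 days after each dose

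*Protocol*

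**What the plan says.** Section 5.7 singles out a small group of local events: "Presence of ulceration and/or scarring at the site of injection and axillary lymphadenopathy of the injection arm(s) are considered to be adverse events". It deems them causally related to study vaccine and of special interest. For two of them it sets a duration: injection-site ulceration (with or without drainage) "and axillary lymphadenopathy will be actively evaluated during each clinic visit through the end of the study". It adds: "These events will be recorded on the Adverse Event screen". No time limit is attached to that recording.

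Other sections set a shorter horizon.

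- Section 3.6.2: "An examination of the injection site will be performed 60 minutes after each study vaccine/placebo administration and at 7 and 28 days after each vaccination".
- Tables 3-1 and 3-2: the row "Site of injection examination" is marked at SD0, SV1, SV2, SV4, SV5 and SV6. It is blank at SV3, SV7, SV8 onward and End of Study. The row for non-serious adverse events has the same pattern.
- Appendix A: SV3, SV7 and SV8 onward list vital signs, TB observation, serious adverse events and blood. End of Study adds a general physical examination that mentions neither injection site nor axilla.
- Section 5.2 collects adverse events "Through the 28-day period following each vaccination all" such events seen or reported; only serious events are collected for the whole study.
- Section 5.6: "The reporting period for all adverse events and adverse reactions is the 28-day post-vaccination follow-up period". No exception is made for events of special interest.

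**The concern.** Safety is the primary objective, and Section 5.7 picks these events out for the longest active watch of any non-serious event in the protocol. The sections that tell a site what to do at a visit do not provide for that watch. Site staff working from the tables or Appendix A would not examine the site or axilla at SV3, SV7 or later visits. Staff who did find something might conclude from Section 5.6 that it falls outside the reporting period. Staff working from Section 5.7 would look for such events and record them. Two sites could each follow the protocol in good faith and produce different data.

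The analysis inherits the problem. If nothing is recorded at a later visit, the table cannot show whether the event was absent or nobody looked. If something is recorded, it is unclear whether it belongs in the primary safety summary.

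**Working it through.** **The rules side by side**

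| Question | Section 5.7 | Rest of the protocol |
|---|---|---|
| How long is the injection site examined? | Each clinic visit to study end | 60 minutes, 7 and 28 days after each dose (3.6.2, Tables 3-1 and 3-2) |
| At which visit is the axilla examined? | Each clinic visit to study end | None listed |
| How long are non-serious events recorded? | No limit stated for these events | 28 days after each dose (5.2, 5.6) |

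Section 5.3 refers the reader to Section 3 for the reporting period of all adverse events. Section 3 holds the schedule with the blank cells, so the cross-reference points away from Section 5.7.

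**Pre-boost gap.** Section 5.3 uses evaluations at SV4, before the booster, to set the baseline for later events. Appendix A lists no site or axillary examination in the pre-vaccination part of SV4; the site examination comes after the injection. A lesion arising between 28 days and the boost (day 168 to 252) has no scheduled pre-boost examination and could be taken as baseline for the second dose.

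**Visits.** Counting each post-baseline column once gives SV1 to SV8 plus End of Study, nine visits. Five have the examination and non-serious event review (SV1, SV2, SV4, SV5, SV6). Four do not: 9 − 5 = 4 (SV3, SV7, SV8, End of Study). Subjects followed longer have more three-monthly visits, all without it.

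**Time.** Two windows of 28 days: 28 + 28 = 56 days. Minimum follow-up is the boost day (168 to 252) plus 6 months (taken as 168 to 182 days):

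- shortest: 168 + 168 = 336 days; 56/336 = 16.7%
- longest: 252 + 182 = 434 days; 56/434 = 12.9%
- at the 36-month maximum in Section 7.6: 36 × 30.4375 = 1,095.75 days; 56/1,095.75 = 5.1%

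**The plan's safety figure.** Section 7.6 gives a 90% probability of seeing at least one event of rate 0.71% among 325 recipients. Check: 1 − (1 − 0.0071)^325 = 0.901. The figure reproduces and is not disputed, but it assumes that every event is recorded. If only a fraction f is captured, the probability becomes 1 − (1 − 0.0071 f)^325:

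| f (assumed) | Probability of at least one recorded |
|---|---|
| 1 | 0.90 |
| 0.75 | 0.82 |
| 0.50 | 0.69 |
| 0.25 | 0.44 |

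The documents give no value for f, so this is illustration only.

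**Which events the primary variable counts.** The abstract and Section 7.4.1 count events recorded over a post-vaccination follow-up period whose length they do not give. Section 5.6 attaches that phrase to 28 days. Yet the same variable includes serious events, which are collected to study end. The phrase therefore does not settle whether a late ulcer or node is counted.

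**The case against.** The strongest defence is that Section 5.7 is the specific rule and should prevail over the general ones. Examining more often than a table lists breaches nothing, and a site that follows Section 5.7 would record late events. This stands in part: the blank cells alone do not forbid the examination. It does not dispose of the reporting limit in Sections 5.2 and 5.6, which has no exception, or of the reference from Section 5.3 back to Section 3.

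There are also real safeguards. Capture resumes at SV4 and runs to 28 days after the boost. Under Sections 5.3 and 5.14, an ulcer or node that starts within a window is followed until it resolves or stabilises, or the study ends. Serious presentations are collected throughout. End of Study includes a physical examination. The schedule is the same in both arms.

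A reader might infer more than the text supports:

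- **That scarring must be checked at every visit.** Section 5.7 names it as of special interest but leaves it out of the active-evaluation sentence.
- **That these events will be under-counted, or late ones lost entirely.** The eCRF is not among the documents, Section 5.7 itself directs recording, and some later examinations do take place.
- **That the share of days outside the windows measures the loss.** That would assume a constant rate over follow-up. Section 5.7 describes solicited events as typically arising soon after vaccination, and no document gives the proportion with later onset.

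**Conclusion.** The protocol contradicts itself. For ulceration and axillary lymphadenopathy, Section 5.7 requires active evaluation to study end, while the schedule and the adverse event reporting period provide for it only through 28 days after each vaccination, and an axillary examination is scheduled nowhere. The consequence is a risk: late-onset events may be missed, or recorded and counted differently between sites, in the primary safety analysis. Events that begin within 28 days of either dose are not in question.

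The extent of the gap is four of nine visit columns, and 83% to 87% of minimum follow-up time (100% less 17% and 13%) outside the two windows. The time figure rests on the protocol's boost window and a 6-month period of 168 to 182 days. Neither figure measures missed events, and no under-count can be computed from the document.

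**What to change.** Reconcile Section 5.7 with Sections 3.6.2, 5.2 and 5.6, Tables 3-1 and 3-2 and Appendix A. To carry out Section 5.7 as written:

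1. Add a row for injection-site (ulceration) and axillary examination at every visit in both tables, with matching text in Section 3.6.2 and Appendix A. Include SV3, SV4 before the boost, SV7, SV8 onward and End of Study.
2. Exempt these events from the 28-day limit in Sections 5.2 and 5.6.
3. State in Section 7.4.1 that they are tabulated by arm through end of study.
4. State whether scarring falls under the same rule.

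If evaluation to study end is not intended, Section 5.7 should be amended to say so; that would also remove the contradiction.

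The cost of the first route is a brief examination and an eCRF field at visits that already take place with vital signs. Section 3.6.3 allows follow-up at home by a clinical research worker or clinician, so whoever attends must be able to examine the site and axilla, and the text should say whether home contacts count as clinic visits for this purpose.

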## 5.8 Subject Diary and Daily Temperature Monitoring

Subjects who receive investigational product will be given, and be instructed in, the operation of a daily adverse event diary and a digital thermometer to be used beginning on the day of each vaccination through 7 days post-vaccination. The daily adverse event diary is a tool to help aid the PI and/or designee to engage in a conversation with the subject about any AEs that may have occurred in-between visits. Entries from the diary card will not be directly recorded onto the electronic case report forms. During scheduled post-vaccination visits, the daily diary will be collected and reviewed by the principal investigator and/or designee at which time any clinical details required for complete understanding of the information recorded will be obtained. Lost diaries or diaries not brought to the scheduled visit will be documented, and the subjects will be queried about the occurrence of clinical events during the 7 days post-vaccination.

Any entry recorded by the subject on the diary card that differs from the opinion of the investigator's evaluation of the event (e.g., the severity level of an event is changed after interviewing the subject) must be explained by notation in the source documentation. Body temperatures below 38° C will not be considered fevers.

## 5.9 Assessing "Seriousness" and Serious Adverse Events

Seriousness refers to the outcome of an adverse event. Seriousness is determined by both the principal investigator and the local medical monitor. If either principal investigator or local medical monitor determines an event to be serious, it will be classified as such. If any of the following outcomes are present then the adverse event is serious:

- It results in **death** (i.e., the AE caused or led to the fatality). Serious does not describe an event which hypothetically might have caused death if it were more severe.
- It was immediately **life-threatening** (i.e., the AE placed the subject at immediate risk of dying. It does not refer to an event which hypothetically may have led to death if it were more severe).
- It required inpatient **hospitalization** or prolonged hospitalization beyond the expected length of stay. Hospitalizations for scheduled treatments and elective medical/surgical procedures related to a pre-existing condition that did not increase in severity or frequency following receipt of study vaccine, are **not** serious by this criterion. Hospitalization is defined as a hospital admission or an emergency room visit for a period greater than 24 hours.
- It resulted in a persistent or significant **disability/incapacity** (i.e., substantial reduction of the subject's ability to carry out activities of daily living).

- It resulted in a **congenital anomaly or birth defect** (i.e., an adverse finding in a child or fetus of a subject exposed to the study vaccine prior to conception or during pregnancy).
- Other **medically important conditions** that may not result in death, threaten life or require hospitalization (i.e., the AE does not meet any of the above serious criteria) may be considered a serious adverse event when, based on appropriate medical judgment, they may jeopardize the subject and require medical or surgical intervention to prevent one of the serious outcomes listed in these criteria (e.g., allergic bronchospasm requiring intensive treatment in an emergency room or at home; blood dyscrasias or convulsions that do not result in hospitalization, or the development of drug dependency or drug abuse).

A **serious adverse event** is an adverse event meeting the outcome criteria for seriousness regardless of relationship to an administered medicinal product.

### 5.10 Assessing Expectedness

Expected adverse events are adverse events consistent with the applicable product information provided by the sponsor (the investigator's brochure for an investigational product). The sponsor, in the person of the local medical monitor, determines expectedness. If the assessment is that the adverse event is **expected** no further action is required. If the local medical monitor's assessment is that the adverse event is **unexpected**, then the event may represent a SUSAR (see Sections 5.10 and 5.11).

### 5.11 Definition of Suspected Unexpected Serious Adverse Reaction (SUSAR)

When an adverse event is judged to be related to an investigational product, such as MVA85A/AERAS-485, and also is judged to be serious and unexpected, it is a SUSAR (suspected unexpected serious adverse reaction) and is subject to expedited reporting.

### 5.12 Reporting of Serious Adverse Events

***Serious adverse events, which include SUSARs, are reported to the sponsor and to the World Wide Safety Center (administered by PPD, Inc.) for the entire study period (see protocol appendices). SUSARs are reported even after the trial is over, if the sponsor, local medical monitor or principal investigator become aware of them.*** The site will be provided with specific reporting procedures including any supplemental reporting forms to be used. Serious adverse events will be reported using a recognized medical term or diagnosis that accurately reflects the event.

Serious adverse events will be assessed by the investigator and the local medical monitor according to their roles (as described in Sections 5.1.2 and 5.1.4) for severity, causal relationship to the study vaccine, and expectedness. The onset and resolution dates of the event and the action taken in response to the event will be documented. If the event has not resolved by the final study visit, it will be documented as "ongoing", however, follow-up of the SAE must continue until resolved. Information recorded must be substantiated in the source documents.

**An SAE Report completed, reviewed and signed by the principal investigator or his/her designee for that event must be emailed or faxed within one business day of the investigative site becoming aware of the event to the local medical monitor, to the World Wide Safety Center at PPD and to the CRO, Triclinium. The initial SAE Report (paper form) should be completed and emailed/faxed even if all information concerning the event is not yet known.**

**Fatal or life-threatening serious adverse events that the investigator suspects are related to the study vaccine should be telephoned to the local medical monitor immediately upon the investigator's awareness of the event. If the local medical monitor is required by the protocol or chooses to suspend enrollment s/he shall immediately create a written memorandum for record to the study file and telephonically notify the sponsor of this act.**

**Contact information for all safety personnel are contained in the Team Contact List which will be stored on site in the Site Regulatory Binder and maintained by the study sponsor.**

Investigators must not wait to collect additional information to fully document the event before notifying the local and global medical monitors of a serious adverse event. The initial notification should include the following (at minimum):

- Protocol number and name and contact number of the investigator
- Subject ID number (and initials and date of birth, if available)
- Date subject received study vaccine
- Serious adverse event(s) and date of event onset
- Current status of subject

Aeras has authorized the PPD World Wide Safety Center to execute its responsibilities for safety report submission to the appropriate regulatory authorities within specific time periods of being notified of the event (within 7 or 15 calendar days depending the character of the SUSAR); therefore, it is important that the investigator submit additional information requested as soon as it becomes available.

Aeras will notify the Data Monitoring Committee of all SUSARs within three working days of becoming aware of an event and will provide all follow-up information in a timely manner.

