### **5.1.3 Local Medical Monitor**

The local medical monitor is the sponsor's representative and is a credentialed physician or surgeon in their country of residence (or geographical region) with the necessary expertise to act in such capacity. The local medical monitor reviews the safety of the product for protocols in a specific region and determines the expectedness. The local medical monitor may make a sponsor's assessment of severity and causality for adverse events that may upgrade the degree of severity and causality determined by the principal investigator. The local medical monitor, like the principal investigator, is blinded for a blinded study.

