The principal investigator and the local medical monitor both determine causality. It is expected that communication and consultation may occur in the assessment of the causality of adverse events. The greatest degree of causal relationship (definite > probable > possible > unlikely

related > not related) determined by either the investigator or local medical monitor after their discussions will determine the ultimate classification of the adverse event. Definite, probable and possible are considered to be related. Not related and unlikely related are considered to be unrelated.

Every effort should be made by the investigator to determine the existence of any pre-existing conditions (e.g., mild nausea or headache on Study Day 0 with onset prior to study vaccination) that must be taken into consideration when assessing causal relationship of an adverse event. Pre-existing conditions should be recorded as baseline history and substantiated by appropriate source documentation. Intermittent conditions such as headaches or menstrual pain may not be present on Study Day 0 but may represent an adverse event if the intensity or duration of the event is worse than usual following study vaccine.

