## **6 STOPPING RULES**

These rules govern the stopping of study vaccine administration at any time during the study. Stopping rules will include:

- Death in any subject that the DMC determines is RELATED to MVA85A/AERAS-485
- An anaphylactic reaction to MVA85A/AERAS-485 in any subject
- A life-threatening adverse event in any subject that the DMC determines is RELATED to MVA85A/AERAS-485
- A serious adverse event that the DMC determines is RELATED to MVA85A/AERAS-485
- A pattern of significant symptoms, physical findings or laboratory abnormalities (adverse events) that, although individually minor, collectively represent a safety concern in the opinion of the investigator or the medical monitor and that the DMC determines are RELATED to MVA85A/AERAS-485

The DMC may permit resumption of study vaccine administration if the study pause was for reasons less severe than those in the DMC stopping rules. The DMC may permit resumption of enrollment if it judges that changes to the study protocol will eliminate or greatly reduce the safety risks specified in the stopping rules. In the absence of study protocol changes the DMC must follow the DMC study stopping rules.

If a decision to resume study enrollment and study vaccine administration is made the DMC will record their judgment in a memorandum to the study file and notify the sponsor, who will then forward the DMC memorandum to the medical monitors and principal investigators. The clinical site will be allowed to resume activities upon receipt of written notification from the sponsor. The appropriate regulatory authority will be informed in writing if the study is stopped and will be informed in writing of the decision by the DMC to resume or discontinue study activities.

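### Section 6 leaves the relatedness decision to the DMC, but outside two scheduled reviews no visible provision requires a death, life-threatening event or SAE that both blinded assessors rate unrelated to reach it

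*Protocol*

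**What the plan says.** Section 6 of the Protocol governs the stopping of vaccine administration throughout the study. Three of its rules depend on a finding by the DMC:

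- On deaths: "Death in any subject that the DMC determines is RELATED to MVA85A/AERAS-485"
- On life-threatening events: "A life-threatening adverse event in any subject that the DMC determines is RELATED to MVA85A/AERAS-485"
- On SAEs in general: "A serious adverse event that the DMC determines is RELATED to MVA85A/AERAS-485"

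Section 5.12 sets the event-driven notice to the DMC: "Aeras will notify the Data Monitoring Committee of all SUSARs within three working days of becoming aware of an event". Section 5.11 defines the term in two steps. Relatedness comes first: "When an adverse event is judged to be related to an investigational product". Seriousness and unexpectedness are then added: "and also is judged to be serious and unexpected, it is a SUSAR".

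On who makes the first causality call, Section 5.5 states: "The principal investigator and the local medical monitor both determine causality". The higher of the two ratings counts. Section 5.1.3 adds: "The local medical monitor, like the principal investigator, is blinded for a blinded study".

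Sections 5.1.5 and 7.8 schedule two DMC safety reviews, one month after the 200th and the 600th subject enrolled. Section 5.1.5 also convenes the DMC whenever vaccination is paused, and lets it unblind as much safety information as it needs.

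**The concern.** The DMC is asked to decide whether an event is related, but the events sent to it one at a time are those that blinded staff have already called related. An event that both assessors rate unlikely related or not related is the one on which an independent, possibly unblinded, view could differ. For that event the Protocol names no required path to the DMC between the scheduled reviews, and none at all after the second.

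Safety is the primary objective. Assessors who judge blinded cases one by one cannot see an imbalance between arms. If an attribution is wrong in the unsafe direction, correcting it while doses are still being given depends on someone choosing to act.

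**Working it through.** The Protocol states no figure on this point, so there is none to reproduce. The check traces every route to the DMC and then dates the scheduled reviews.

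**Routes to the DMC**

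| Route | Section | Required? | Reached by an event that both blinded assessors rate unrelated? |
|---|---|---|---|
| SUSAR notice | 5.12, 5.11 | Yes | No: needs a related rating, and unexpectedness |
| Mandatory pause by investigator or local medical monitor | 5.1.1.1, 5.1.3.1, 5.1.5 | Yes | No: covers expected SAEs and event patterns too, but only if rated at least possibly related |
| Investigator's pause on suspicion of significant risk | 5.1.1, 5.1.5 | No | Possibly |
| Global medical monitor unblinds a selected SAE | 5.1.4, 5.1.5 | No | Possibly: 5.1.5 counts this monitor's pause as convening the DMC, but 5.1.4 gives the role no pausing rule |
| DMC, once convened, looks at all AEs and SAEs | 5.1.5 | No | Yes, but something else must convene it |
| Scheduled reviews | 5.1.5, 7.8 | Yes | Yes, on two occasions |

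Only the last row is both required and open to such an event.

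There are two further mismatches along these routes. Section 5.1.1.1 lets the investigator, with the local medical monitor's agreement, resume after the investigator's own pause if the causality assessment is lowered. Section 5.1.5 says any pause by the investigator convenes the DMC. The global medical monitor's place in Section 5.1.5 has no counterpart in Section 5.1.4.

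**Timing of the scheduled reviews**

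Inputs: 650 subjects (Section 2.2); 21 months of enrolment and a 36-month maximum (Section 7.6); booster at day 168 to 252 (Appendix A). Assumptions: uniform accrual, no dropout, 30.4375 days per month.

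- Review 1: 200/650 × 21 + 1 = 7.5 months.
- Review 2: 600/650 × 21 + 1 = 20.4 months.
- Gap between reviews: 12.9 months. From review 2 to month 36: 15.6 months.
- Booster lag: 168/30.4375 = 5.52 months to 252/30.4375 = 8.28 months.
- Last booster: 21 + 5.52 = 26.5 months to 21 + 8.28 = 29.3 months.
- Share boosted by review 2: (20.38 − 5.52)/21 = 71% to (20.38 − 8.28)/21 = 58%.
- Share of boosters after review 2: 29% to 42%, or about 190 to 275 of 650 subjects across both arms.

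Vaccination thus continues for about 6 to 9 months after the last scheduled review.

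**The case against.** The strongest reply is that the routing was chosen. The version 4.0 change log explains that only SUSARs go to the DMC at once and that other SAEs are summarised at scheduled meetings. Section 6 requires a DMC finding before stopping; it does not say that the DMC adjudicates every event as it happens. This stands as an account of intent and argues against putting every SAE on the three-day clock. It does not cover the period after the second review, when no scheduled meeting remains.

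The safeguards are also real. Sites notify both the local and the global medical monitor of SAEs, and the global monitor may unblind them. The local monitor may raise a causality rating, the higher rating governs, and the possible category is broad enough to include events for which the evidence leans against causation. All this makes a missed event less likely. None of it obliges anyone to send the DMC an event that both assessors rate unrelated.

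Some stronger readings are tempting, but the documents do not support them:

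- *The DMC is the only body able to unblind, or between reviews can only confirm or downgrade.* The global medical monitor can unblind, and a DMC convened for any reason may review everything and upgrade an event.
- *About 61% of follow-up is unprotected.* Mean follow-up is 36 − 10.5 = 25.5 months and (36 − 20.39)/25.5 = 61% does fall after review 2. But Section 6 governs vaccination, and 26% to 37% of follow-up ((36 − 29.3)/25.5 to (36 − 26.5)/25.5) comes after the last booster, when nothing is left to stop. That leaves 24% to 35%.
- *The DMC would be sent almost no events.* No related SAE in 1,870 earlier subjects gives an upper bound of 1 − 0.05^(1/1870) = 0.16%. Most earlier recipients were infants and children, only 80 were HIV-positive, and blinded staff may also rate placebo events related. The bound cannot size SUSAR traffic in this trial.
- *Table S2 shows harm that was missed.* SAEs in subjects not on ART were 2/69 on placebo and 9/67 on vaccine. Totals were 17 in each arm, the ART group went the other way (15/256 and 8/257), and neither timing nor relatedness is given. This is no evidence of harm, and results could not have informed the plan.

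Finally, the SAE reporting scheme in Appendix B is a figure that is not shown. A broader route could appear there, although the version 4.0 rationale makes that unlikely.

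**Conclusion.** The point holds as a gap in routing. Three Section 6 rules need a DMC judgement on events that, outside two scheduled reviews, no visible provision obliges anyone to send it unless a blinded assessor has already rated them at least possibly related. The discretionary routes reduce the gap without removing it.

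The best measure of its size is the 29% to 42% of boosters due after the last scheduled review. That range comes from the booster window and rests on uniform accrual and no dropout; slower or uneven accrual would move it. The number of events affected cannot be estimated from the plan. The finding does not say that any stopping rule is wrong, and it does not show that an event was missed. The passages should be reconciled, because safety is the primary objective and the remedy is cheap.

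**What to change.** Reconcile Sections 5.1.1.1, 5.1.4, 5.1.5, 5.12 and 6 so that the events Section 6 asks the DMC to judge reach it. One way that keeps the version 4.0 intent:

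- forward to the DMC the existing reports of deaths and life-threatening events, whatever the blinded causality and expectedness ratings;
- send other SAEs as a periodic listing that continues after the second review until the last booster.

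The same revision should settle whether an investigator's pause always goes to the DMC, and whether the global medical monitor can pause vaccination or report to the DMC. Which answer is right is for the sponsor and the DMC to decide. The example changes who receives reports and leaves every stopping criterion as it is.

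The cost is a protocol wording change and a little more DMC paperwork. Sites already complete SAE reports within one business day, so no new data collection is needed.
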